# Laparoscopic versus open adhesiolysis for small bowel obstruction - a multicenter, prospective, randomized, controlled trial

**DOI:** 10.1186/1471-2482-14-77

**Published:** 2014-10-11

## Abstract

**Background:**

Laparoscopic adhesiolysis is emerging as an alternative for open surgery in adhesive small bowel obstruction. Retrospective studies suggest that laparoscopic approach shortens hospital stay and reduces complications in these patients. However, no prospective, randomized, controlled trials comparing laparoscopy to open surgery have been published.

**Methods/Design:**

This is a multicenter, prospective, open label, randomized, controlled trial comparing laparoscopic adhesiolysis to open surgery in patients with computed-tomography diagnosed adhesive small bowel obstruction that is not resolving with conservative management. The primary study endpoint is the length of postoperative hospital stay in days.

Sample size was estimated based on preliminary retrospective cohort, which suggested that 102 patients would provide 80% power to detect a difference of 2.5 days in the length of postoperative hospital stay with significance level of 0.05. Secondary endpoints include passage of stool, commencement of enteral nutrition, 30-day mortality, complications, postoperative pain, and the length of sick leave. Tertiary endpoints consist of the rate of ventral hernia and the recurrence of small bowel obstruction during long-term follow-up. Long-term follow-up by letter or telephone interview will take place at 1, 5, and 10 years.

**Discussion:**

To the best of our knowledge, this trial is the first one aiming to provide level Ib evidence to assess the use of laparoscopy in the treatment of adhesive small bowel obstruction.

**Trial registration:**

ClinicalTrials.gov identifier:
NCT01867528. Date of registration May 26th 2013.

## Background

Small bowel obstruction (SBO) is a common surgical emergency most frequently caused by adhesions. A large portion of adhesive SBO resolve by nonoperative methods such as fasting and ingestion of an oral contrast-media, while a significant number of patients will need emergency surgery
[1]. For decades open surgery has been the gold standard in treating adhesive SBO. Now that laparoscopic surgery has been established as a first line option in many elective indications such as colorectal surgery, fundoplication, and cholecystectomy for example, laparoscopy is emerging also as a viable alternative in emergency surgery.

If SBO is caused by one adhesive band, the surgical treatment is straightforward - cutting the band causing obstruction. Laparoscopic approach seems ideal for such a procedure, preventing the morbidity of a laparotomy incision. First publications describing laparoscopic adhesiolysis in SBO are from the 1990’s
[2]. Since then several retrospective series have been published, and a recent meta-analysis pooled patients from four studies, including a total of 334 patients
[3]. Meta-analysis showed that patients treated by the laparoscopic approach had less complications, and faster return of bowel function
[3]. However, there are no prospective randomized trials comparing open approach to laparoscopy. Furthermore, previous retrospective studies have a selection bias because the easiest cases are selected for laparoscopic approach. One of the drawbacks of laparoscopic approach is a concern for iatrogenic bowel perforation. In one report, the rate of bowel lesion in laparoscopic adhesiolysis was 6.6%, and only 84% were detected during the operation
[4].

## Methods/Design

### Objective

The objective of this trial is to compare open surgery to laparoscopic adhesiolysis in patients with computed tomography-diagnosed adhesive SBO that is not resolved by nonoperative means. The hypothesis is that laparoscopic approach shortens the length of hospital stay without increasing complications.

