### Primary endpoint

– Length of post-operative hospital stay (days)

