### Secondary endpoints

– Passage of stool (post-operative days)

– Commencement of enteral nutrition (post-operative days)

– 30-day mortality

– Complications (all causes), graded by Clavien-Dindo classification

– Number of participants with iatrogenic small bowel lesions

– Number of participants with readmission(s)

– Number of participant with failure to resolve obstruction

– Pain scores on the Visual Analog Scale

– Length of epidural catheter analgesia (days)

– Total need of opioids in milligrams

– Length of sick leave (days)

– Conversion rate (laparoscopic group)

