### Data collection and analysis

Data will be collected by using an electronical case report form, and statistically analyzed in the main research center (Helsinki) once the trial is completed. Continuous variables will be compared using t-test or Mann–Whitney-U-test. Categorical variables will be compared using Fischer’s exact-test or Chi-square-test. Groups will be analyzed as intention-to-treat. An interim analysis will be made when 52 patients have been randomized and treated.

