### Sample size calculation

Based on preliminary retrospective analysis on laparoscopic and open adhesiolysis we have estimated the standard deviation to be 3.75 days in laparoscopic group and 5 days in open surgery group. Sample size is calculated to be able to demostrate 2.5 day difference in the post-operative length of stay. 102 patients are needed to achieve 80% power with a significance level of 0.05.

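### The hypothesis includes no increase in complications, but the trial is sized only for length of stay and plans only difference tests, so it cannot support that half

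*Protocol article*

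**What the plan says.** The Objective section of the protocol article gives a two-part hypothesis: "The hypothesis is that laparoscopic approach shortens the length of hospital stay without increasing complications".

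Other sections bear on the two parts as follows:

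- **Primary endpoint:** length of post-operative hospital stay is the only one.
- **Sample size calculation:** the trial is sized on stay alone: "Sample size is calculated to be able to demostrate 2.5 day difference in the post-operative length of stay". The total is 102 patients, with 80% power at a significance level of 0.05.
- **Secondary endpoints:** the list of 12 includes "Complications (all causes), graded by Clavien-Dindo classification", and also iatrogenic small bowel lesions and 30-day mortality.
- **Data collection and analysis:** "Categorical variables will be compared using Fischer’s exact-test or Chi-square-test".
- **Background:** iatrogenic perforation is named as a concern with laparoscopy. One report is cited in which "the rate of bowel lesion in laparoscopic adhesiolysis was 6.6%, and only 84% were detected during the operation".

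The article gives no planning rate for complications, no tolerable increase and no statement of how a non-significant complications result would be interpreted.

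**The concern.** The two halves of the hypothesis need different kinds of evidence. A shorter stay can be shown by a significant difference test. Absence of an increase cannot be shown by a non-significant one, because such a result is also what a small trial usually returns when a real increase exists. To support that half, the confidence interval would have to exclude an increase large enough to matter.

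The question is a live one for this trial. The Background raises bowel injury as a drawback of laparoscopy and says the earlier retrospective comparisons suffer from selection of the easiest cases. The article also presents the trial as the first to aim at level Ib evidence. If stay is shorter and the complications test is non-significant, readers could take the whole hypothesis as supported even though the data remained compatible with a material excess of complications.

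**Working it through.** **Inputs from the protocol.** Standard deviations 3.75 and 5 days, difference 2.5 days, 80% power, significance level 0.05, N = 102 (Sample size calculation); 1:1 allocation, hence 51 per arm (Randomization procedure); 6.6% bowel lesions with laparoscopy (Background).

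**Assumptions, not in the protocol.** Open-arm complication rates of 10% to 40%; all comparator rates for bowel lesions; all margins.

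**1. The plan's own figure.** The pooled SD is √((3.75² + 5²)/2) = √19.53 = 4.42 days. The normal formula gives 2 × (1.96 + 0.842)² × 19.53 / 2.5² ≈ 49.1, so 50 per arm. The two-sided t-test version gives 50.03, so 51 per arm and 102 in total, with power 0.808. The stated 102 is reproduced and is not in question.

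**2. Power for a true 10-point rise in complications, 51 per arm, two-sided 0.05.** The normal approximation to the chi-square test is Φ[(d − 1.96·SE₀)/SE₁], where SE₀ = √(2p̄(1−p̄)/51) and SE₁ = √((p₁(1−p₁) + p₂(1−p₂))/51). For 20% versus 30%, p̄ = 0.25, SE₀ = 0.0857 and SE₁ = 0.0852. Power is Φ[(0.10 − 0.168)/0.0852] = Φ(−0.80) = 0.21. Fisher power is by full enumeration of the two binomials.

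| Assumed open rate | Laparoscopic rate | Normal approximation | Fisher exact |
|---|---|---|---|
| 10% | 20% | 29% | 20% |
| 20% | 30% | 21% | 16% |
| 30% | 40% | 18% | 14% |
| 40% | 50% | 17% | 14% |

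By the normal approximation, the rise detectable with 80% power is about 23 to 27 points over the same range.

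**3. Bowel lesions.** At 6.6%, 51 × 0.066 ≈ 3.4 affected patients are expected in an arm. For an assumed doubling from 6.6% to 13.2%, power by enumeration is 10% (Fisher) or 19% (uncorrected chi-square). If 6.6% is kept as the laparoscopic rate and 3.3% is assumed for open surgery, power is 3% or 10%.

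**4. Precision.** With equal rates p, the 95% half-width is 1.96 × √(2p(1−p)/51). At 6.6% it is 1.96 × 0.0492 = 0.096, about 10 points. At an assumed 30% it is 1.96 × 0.0907 = 0.178, about 18 points.

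**5. Could a margin set elsewhere rescue the claim?** Non-inferiority at one-sided 0.025 with 80% power and equal true rates needs (1.96 + 0.842)² × 2p(1−p)/m² per arm. For a 10-point margin at 30%, this is 7.85 × 0.42 / 0.01 ≈ 330 per arm, or 660 in total. Over assumed rates of 10%, 20%, 30% and 40% the totals are 284, 504, 660 and 754, and 102 patients give 39%, 24%, 20% and 18% power. At a 20-point margin the totals are 72, 126, 166 and 190, so 102 patients suffice only near a 10% rate.

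**The case against.** The strongest reply is that this is an ordinary design: one efficacy endpoint carries the sample size, and complications are followed as secondary safety outcomes. On that view the phrase about complications is a clinical expectation, not a formal co-primary claim. The endpoint lists and the sample size fit that reading, and few surgical trials are powered for complications. This stands to the extent that the design is not an error and nothing here calls for a larger trial. It does not remove the mismatch, because the Objective section puts the phrase inside the stated hypothesis.

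A second reply is that margins, confidence intervals and rules of interpretation belong in a statistical analysis plan, which is not shown. Their absence from the article is not held against it. But N is fixed here, and at the assumed rates no analysis plan could make 102 patients adequate for a margin of 10 points or less.

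A reader might go further and infer that, as written, a shorter stay with a non-significant complications test confirms the whole hypothesis. The protocol contains no such decision rule. It says only that categorical variables will be compared, so that reading is an inference. Nor does the trial have no power for complications: none was planned, and the actual power is low.

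Quoting Fisher power alone would also be selective, since chi-square is allowed and does somewhat better, although Fisher would be the usual choice at the rarest rates. Both are given above, and both are low.

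**Conclusion.** The point holds as a mismatch between the stated hypothesis and what the design can show. The half about complications has no planned power, and the only analysis stated for it is a test of difference, so a non-significant result could not support it.

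For a true 10-point rise, the planned tests would miss the increase in roughly 70% to 85% of trials. The exact size rests on assumed rates: the protocol supplies only the 6.6% figure, for laparoscopy, from one report. The conclusion is stable over open-arm rates of 10% to 40% and over either permitted test. It would weaken only if a margin as wide as 20 points were acceptable and complications were near 10%.

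The length-of-stay calculation is sound. How the investigators would interpret a non-significant result is not documented. The hypothesis should be reworded; this is not a fault in the sample size.

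**What to change.** - **Objective:** limit the confirmatory hypothesis to shorter post-operative stay with laparoscopy.
- **Objective and Data collection and analysis:** name complications, iatrogenic bowel lesions and 30-day mortality as secondary safety outcomes, reported as risk differences with 95% confidence intervals. State that absence of a significant difference will not be interpreted as absence of an increase.

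The cost is a few sentences. N stays at 102, and endpoints, data collection and conduct do not change. The downside is a weaker safety claim.

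As a separate and optional gain in efficiency, the worst Clavien-Dindo grade per patient could be compared with a centre-stratified rank test, since the grades are ordered. The protocol does not say that grades will be tested as unordered categories, and a rank test could not show absence of an increase either, so the point does not depend on this.

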### Ethics and permissions

This study will be conducted in accordance with the principles of the Declaration of Helsinki and ‘good clinical practice’ guidelines. The research plan has been evaluated and approved by the local institutional ethics committee of the main research center (Helsinki University Central Hospital, Ethics Committee, Department of Surgery). The research plan has further been approved by each participating centers’ institutional review board (Helsinki University Central Hospital, Vaasa Central Hospital, Turku University Hospital, Oulu University Hospital, Tampere University Hospital, Päijät-Häme Central Hospital). CONSORT 2010 checklist is shown in Additional file
1.

### Patient evaluation and selection

Patients with computed tomography-confirmed SBO will be eligible for the study. If no exclusion criteria are present, nasogastric tube is inserted and the patient is admitted to the emergency surgery ward. If the obstruction does not resolve within 12 hours, an oral water-soluble contrast (Gastrografin®) is used. If the contrast has not advanced to the colon within 8 hours and the patient has no signs of spontaneous resolution of obstruction, surgical intervention is considered necessary and the patient is randomized to either open or laparoscopic surgery. The oral water-soluble contrast study has been shown to have 97% sensitivity and 96% specificity in predicting nonoperative resolution of adhesive SBO
[5]. Patients can alternatively undergo nonoperative management by fasting and nasogastric tube only if oral water-soluble contrast is contraindicated or not available. If SBO in these patients is not resolved within 48 hours, they are included in the study (Figure 
1).

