## Discussion

While laparoscopy has become the treatment-of-choice in acute cholecystitis, acute appendicitis, and perforated peptic ulcer, there are still areas of emergency surgery that are under debate
[6,7]. It has been suggested that purulent peritonitis caused by acute diverticulitis can be treated by laparoscopic lavage
[8], and randomized studies are on their way to either prove or disprove this approach
[9,10].

As laparoscopic surgery is becoming more common in emergency surgery, adhesive SBO is the obvious next target for a laparoscopic approach
[1]. Although there are several retrospective series, and meta-analyses comparing open approach to laparoscopy, there are no prospective, randomized studies. A search for ongoing trials reveals that, except for this trial, there are no other prospective, randomized trials enrolling patients at the moment of writing. Although previous retrospective series have shown association of less complications and shorter hospital stay with the laparoscopic approach, all previous retrospective series are more or less biased as the easiest cases are selected for laparoscopic approach.

This trial aims to provide level Ib evidence for the use of laparoscopy in the treatment of adhesive SBO that is not resolving by conservative means. Two large meta-analyses have shown that the advancement of oral contrast agent (Gastrografin) to the colon predicts that the obstruction would resolve with 0.97 sensitivity and 0.96 speficity
[5,11]. Optimal timing of the abdominal radiograph to predict the success of nonoperative management is unknown
[5]. In this study, the sensitivity, specificity, positive and negative likelihood ratios for waiting 4–8 hours were similar to waiting 24 hours before abdominal radiograph is carried out
[5,11]. Thus, there appears to be no advantage of waiting more than 4–8 hours. In this trial, if the oral contrast agent is not detected in the colon after 8 hours the conservative management is considered a failure and operative management is warranted. Further, the intestine is decompressed using a nasogastric tube for a minimum of 12 hours before commencing the oral contrast agent study. Thus, in total, the nonoperative management trial takes at minimum 20 hours.

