Because there are several exclusion criteria in this trial, the patients are selected, and the results will not be applicable to all patients presenting with an adhesive SBO. These exclusion criteria, however, should not be regarded as absolute contraindications for laparoscopic approach. Many of the exclusion criteria are relative contraindications (peritonitis, suspicion of other cause than adhesions, pregnancy, wide diffuse adhesions, peritoneal carcinosis) or predictors of failure of laparoscopic approach (endometriosis, earlier generalized peritonitis, over 3 open procedures, radiotherapy, vascular procedures)
[12]. Furthermore, earlier obesity surgery is an indication for laparoscopic approach, and these patients are excluded because we do not think it is ethical to randomize them for open approach. Some of the exclusion criteria (age >95 years, earlier abdominal surgery within 30 days, patient living in an institutional care, or prior hospital stay of over 1 week) were included to reduce the morbidity of the patients included in the study, as inclusion of a few of these patients in one of the arms would create a strong bias (i.e. the length of stay would be longer because of the morbidity of the patients, not because of the approach used).

The trial has been recruiting since summer 2013. Enrollment of the patients is estimated to last for 4–5 years and primary end-point results are estimated to be available in 2018.

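### The primary comparison of post-operative stay is unadjusted although randomisation is stratified by centre and age is known before allocation: valid, but a cheap gain in precision is left unused

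*Protocol article*

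**What the plan says.** All references are to the protocol article.

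- **Data collection and analysis.** "Continuous variables will be compared using t-test or Mann–Whitney-U-test". The same section says "Groups will be analyzed as intention-to-treat" and schedules an interim analysis at 52 patients. It names no covariate or stratum term.
- **Randomization procedure.** Allocation is 1:1 in blocks, stratified by centre and nothing else. The envelope is opened only once eligibility is confirmed. The ethics section lists six hospitals.
- **Eligibility criteria.** Age (18 to 95) and number of earlier open abdominal operations (three or more excludes) both have to be checked, and both still vary among eligible patients.
- **Patient evaluation and selection; Discussion.** There are two routes to randomisation. On the contrast route, "the nonoperative management trial takes at minimum 20 hours". Where contrast is contraindicated or unavailable, a longer period applies: "If SBO in these patients is not resolved within 48 hours, they are included in the study".
- **Discussion.** Some exclusions are justified by the worry that, if a few such patients fell in one arm, "the length of stay would be longer because of the morbidity of the patients, not because of the approach used".
- **Sample size calculation.** "we have estimated the standard deviation to be 3.75 days in laparoscopic group and 5 days in open surgery group"; the target is a 2.5-day difference with 102 patients, 80% power and a significance level of 0.05.

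**The concern.** Neither named test can take a covariate. If centres differ in how long they keep patients, or if older patients stay longer, that variation stays in the error term. Ignoring the stratification factor then makes the standard error larger than it need be, and any chance imbalance in age stays in the one estimate the trial will produce. The design has little slack: 51 per arm gives just over 80% power and 50 per arm falls just short. A modest gain from information that must be ascertained anyway is therefore worth having. At stake is the width of the confidence interval for the primary result, not its validity.

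**Working it through.** **Inputs from the protocol.** SDs 3.75 (laparoscopic) and 5 (open), difference 2.5 days, 51 per arm, significance level 0.05 (taken as two-sided, since one-sided gives only 39 per arm), six centres.

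**Assumed, not in the protocol.** The share R² of variance in stay that the covariates explain; the share p of patients on the 48-hour route; the effect g of that route on post-operative stay.

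**1. The plan's own figure.** Normal approximation: n per arm = (3.75² + 5²)(1.960 + 0.842)² / 2.5² = 39.06 × 7.849 / 6.25 = 49.06, so 50 per arm or 100 in total. With the unequal-variance (Welch) t-test, power is 79.9% at 50 per arm and 80.7% at 51. The stated 102 is reproduced.

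**2. Unadjusted precision.** SE = √(39.06 / 51) = 0.875 days.

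**3. Adjustment, ignoring its cost.** SE is multiplied by √(1 − R²).

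**4. Adjustment, with its cost.** The fullest model adds eight terms: five centre indicators, age, earlier operations and route. Residual degrees of freedom are 102 − 2 − 8 = 92. Centre is nearly balanced by the stratified blocks. The other three covariates are not, and their chance correlation with arm raises the variance by about 3/100, so SE is also multiplied by √1.03. Power then comes from the non-central t with 92 degrees of freedom.

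| Assumed R² | SE, step 3 (days) | Power, step 3 | SE, step 4 (days) | Power, step 4 |
|---|---|---|---|---|
| 0 | 0.875 | 80.7% | 0.888 | 79.5% |
| 5% | 0.853 | 82.6% | 0.866 | 81.5% |
| 10% | 0.830 | 84.6% | 0.843 | 83.5% |
| 20% | 0.783 | 88.5% | 0.794 | 87.6% |

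Simulation of the eight-term model (six equal centres with no true centre effect and 15% on the 48-hour route, all assumed) agrees to within about a point: roughly 79 to 80%, 81 to 82%, 83 to 84% and 87 to 88%. At R² = 5% the adjusted interval was still wider than the unadjusted one in some 41 to 45% of simulated trials, so a gain on average is not a gain every time.

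**5. Entry route alone.** R² = p(1 − p)g² / 19.53, where 19.53 = 39.06 / 2 is the mean variance. For p = 10% and g = 2 days: 0.09 × 4 / 19.53 = 0.018. Before any cost, power moves from 80.7% to 81.4%, less than one point. The SD of the shift in the estimated difference from chance imbalance in route is g√(2p(1 − p)/51) = 2 × √(0.18/51) = 0.12 days, against an SE of 0.875. Over p = 5 to 30% and g = 1 to 3 days, R² runs from 0.002 to 0.097.

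**The case against.** The strongest reply is that nothing here is wrong. An unadjusted comparison of randomised arms keeps its type I error, and the sample size was calculated for exactly that comparison. The sentence on tests is a general one in a condensed article, and a statistical analysis plan that is not shown may name an adjusted model. The first part stands in full. The second stands in part: the sentence does not rule out adjustment elsewhere, but it does name the tests, so it is the natural place for the change.

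Three stronger readings are tempting, and the protocol does not support them.

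- *The two entry routes distort the comparison.* A reader might infer this from the 20-hour and 48-hour periods. But the 48-hour route is an exception with no stated frequency, the 20 hours is a minimum, pre-operative time is not counted in the endpoint, and no passage links delay to post-operative stay. Randomisation also spreads both routes over both arms.
- *The protocol's own worry about sick patients is left unanswered.* The Discussion voices that worry about particular groups, which it then excludes. Number of open procedures appears there as a predictor of laparoscopic failure, not of longer stay.
- *The precision is free and certain.* The eligibility list gives thresholds. It does not show that the exact number of operations is on the case report form. Adjustment also costs degrees of freedom and returns nothing if the covariates do not predict stay.

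**Conclusion.** The point holds as an optional but worthwhile improvement in efficiency. The planned test is valid and the 102 patients match it. Adding centre, age and, if wanted, two minor terms would take power from 80.7% to about 81%, 84% or 88% if the covariates explain 5%, 10% or 20% of the variance in stay, and would lose about one point if they explain none. These R² values are assumptions, because the protocol gives no covariate-outcome relation and no centre effect. The case rests on centre, because it is the stratification factor, and on age, because it must be known before allocation. Entry route alone would add under one point at an assumed 10% share and 2-day effect. It should not be read as a source of bias.

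**What to change.** In the data-analysis section, name as the primary analysis a linear regression of post-operative stay (days) on arm, centre and age, by intention to treat. Number of earlier open abdominal operations and entry route may be added as minor terms. Use heteroscedasticity-robust standard errors, because the sample size section assumes unequal SDs (3.75 and 5). A linear model keeps the result on the scale of the 2.5-day difference for which the trial is sized. Fix the covariate list before the 52-patient interim analysis, and keep the unadjusted test as a sensitivity analysis.

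Cost: wording, plus six model terms for centre and age (eight with the optional two) out of 102 patients. Confirm that the case report form holds the number of earlier operations and the entry route before listing them. No patient, visit or clinical rule changes.
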